### Trial Duration, Schedule and Follow-up

The primary endpoint is acute toxicity of carbon ion radiotherapy observed within 30 days of study treatment.

Patients are scheduled for follow-up visits every 4 weeks after completion of carbon ion radiotherapy for the first 3 months, thereafter in 2-months intervals or as needed clinically including contrast-enhanced MRI as well as thorough clinical-neurological and haematological assessment. These follow-up visits are in line with standard care outside of clinical trials.

The last patient included into the study will be followed for at least 3 months after study treatment. This is considered the final study visit. All other patients will be followed regularly as described in detail until death or until 3 months after LPI.

The overall duration of the trial is expected to be approximately 24 months.

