### Statistical calculations for trial sample size

#### Study hypothesis

The study is designed to demonstrate that carbon ion radiotherapy is safe for the treatment of HCC. The aim of the study is to evaluate the optimal dose tolerated with respect to toxicity.

Unacceptable toxicity (DLT) is defined as any irreversible grade 4 toxicity during a time frame of 30 days as classified by CTCAE version 4.0.

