### Statistical Methods

#### Sample Size Calculation

The calculation of sample size for the PROMETHEUS-01 trial is based on the traditional dose escalation scheme. DLT are considered any irreversible Grade 4 toxicity classified by CTCAE version 4.0 after study treatment.

Patients are treated in cohorts of three each receiving the same dose.

For observation of DLT, patients are observed for 30 days after study treatment. If the last patient of the cohort is observed 30 days after study treatment, patients of the next cohort may be recruited.

If none of the three patients shows a DLT, the next cohort of three patients receives the next higher dose as described above.

Otherwise, if at least one patient of the cohort develops a DLT (1/3), a second cohort of three patients is treated at the same dose level without escalating the dose.

If exactly one out of the six patients (1/6) treated exhibits DLT, the trial continues as planned at the next higher dose level.

If two or more patients out of the six exhibit a DLT, the dose escalation stops at that level and the next lower level is considered as the MTD. When the escalation has stopped, additional patients will be treated at the MTD to a total of nine patients.

This trial is conducted to choose the MTD of carbon ion radiotherapy between five dose levels. Therefore the sample size at maximum is 33 patients (4 dose levels with at maximum 6 patients and 9 patients at the MTD).

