#### Analysis Variables

Primary endpoint is the MTD chosen between the five dose limits based on the traditional dose escalation scheme. Any unpredictable of irreversible grade 4 toxicity possibly, probably or definitely related the study treatment occurring 30 days after completion of study treatment is considered as dose limiting toxicity.

Secondary endpoints are the collection of safety data on the dose levels used in this trial as well as response, progression-free survival, and overall survival.

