### Statistical Methods

#### Confirmatory Analysis

No confirmatory statistical analysis will be performed. The MTD is determined according to the traditional dose-escalation scheme for Phase I trials in oncology.

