#### Descriptive Analysis

Descriptive summary tables will be presented on baseline patient characteristics as well as for all safety parameters by dose level. Absolute and relative frequencies are reported for all toxicities of the CTC list (NCI CTC-AE Version 4.0) by distinguishing the grading and the assessment of the relation to treatment. Within this study, dose limiting toxicities (DLTs) are defined as any grade IV toxicity according to CTCAE Version 4.0 possibly, probably or definitely associated to study treatment during 30 days after completion of therapy.

A description of the individual load of toxicity of each patient will be made separately using individual descriptions eventually supported by graphical methods.

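### The dose-limiting toxicity is defined in three conflicting ways, so the same patients can lead to different escalation decisions and a different MTD

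*Protocol article*

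**What the plan says.** All four statements of the DLT use grade 4 events under CTCAE version 4.0 and a window of about 30 days. They differ in what else is required.

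- **Study hypothesis:** "Unacceptable toxicity (DLT) is defined as any irreversible grade 4 toxicity during a time frame of 30 days as classified by CTCAE version 4.0". The event must be irreversible; no relatedness is required.
- **Sample Size Calculation:** "DLT are considered any irreversible Grade 4 toxicity classified by CTCAE version 4.0 after study treatment". In substance this is the same.
- **Analysis Variables:** "Any unpredictable of irreversible grade 4 toxicity possibly, probably or definitely related the study treatment occurring 30 days after completion of study treatment". The event must be at least possibly related. The word *of* is probably a slip for *or*, so that an unpredictable event qualifies as well as an irreversible one.
- **Descriptive Analysis:** "dose limiting toxicities (DLTs) are defined as any grade IV toxicity according to CTCAE Version 4.0 possibly, probably or definitely associated to study treatment". The event must be at least possibly related; irreversibility is not required.

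Sample Size Calculation also holds the decision rule. With no DLT in three patients the dose goes up. With at least one, three more patients are treated at the same dose. With exactly one in six the dose goes up. Finally, "If two or more patients out of the six exhibit a DLT, the dose escalation stops at that level", and the level below becomes the MTD. Analysis Variables makes that MTD the primary endpoint. Confirmatory Analysis adds only that "The MTD is determined according to the traditional dose-escalation scheme for Phase I trials in oncology".

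**The concern.** A 3+3 scheme turns a DLT count into a decision but does not say what a DLT is. The pointer in Confirmatory Analysis therefore does not settle which wording applies.

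The wordings differ on two separate axes, reversibility and relatedness, and none of them is always the strictest. No wording can be taken as a safe default. Under the irreversible-only wording, a dose that causes related, life-threatening but reversible toxicity can be escalated. Under the wording without a relatedness condition, events from the underlying disease can halt escalation and set the MTD too low.

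Unrelated grade 4 events are plausible here: the listed eligibility criteria contain no liver-function limit and admit Karnofsky scores down to 60. If the choice of wording is made once events have been seen, the primary endpoint, and the dose carried into later trials, depends on that choice.

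**Working it through.** **The plan's own figure.** Four levels at no more than 6 patients plus 9 at the MTD gives 4 × 6 + 9 = 33. This reproduces the stated maximum, and it does not depend on the DLT definition.

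**How each type of grade 4 event is counted** (reading *of* as *or* in Analysis Variables):

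| Event | Study hypothesis / Sample Size Calculation | Analysis Variables | Descriptive Analysis |
|---|---|---|---|
| Irreversible, related | DLT | DLT | DLT |
| Irreversible, unrelated | DLT | no | no |
| Reversible, related, unpredictable | no | DLT | DLT |
| Reversible, related, expected | no | no | DLT |

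If the word unpredictable is struck out, three definitions remain: irreversible whatever the cause; irreversible and related; any grade 4 and related.

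**Two worked cohorts.**

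- Two of the first three patients have reversible, expected, related events. Descriptive Analysis counts 2/3; a second cohort is treated, the count is at least 2/6, and escalation stops. The other three sections count 0/3, and the dose goes up.
- Two of the first three have irreversible, unrelated events. Study hypothesis and Sample Size Calculation lead to a stop. Analysis Variables and Descriptive Analysis count 0/3, and the dose goes up.

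This much follows from the wording alone.

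**Size, under assumed risks.** Under the rule as written, a level with DLT risk p is passed with probability

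P(escalate) = (1−p)³ + 3p(1−p)⁵,

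and all five levels are cleared with the product over levels. For example, at p = 10%: 0.9³ + 3 × 0.1 × 0.9⁵ = 0.729 + 0.177 = 0.906.

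Inputs, all assumed:

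- r, the risk of a related grade 4 event at each level;
- half of these events are irreversible;
- b, the risk of an unrelated grade 4 event, half of these irreversible;
- no unpredictable events.

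Then p = r for Descriptive Analysis and p = 1 − (1 − r/2)(1 − b/2) for Sample Size Calculation. Probability of clearing all five levels:

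| r by level | Descriptive Analysis | Sample Size Calculation, b = 0 | b = 5% | b = 10% |
|---|---|---|---|---|
| 1/2/3/4/5% | 0.941 | 0.984 | 0.915 | 0.804 |
| 2/4/6/8/10% | 0.799 | 0.941 | 0.848 | 0.725 |
| 5/10/20/30/45% | 0.072 | 0.466 | 0.376 | 0.293 |

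In the first row the order of the two definitions reverses once b reaches 5%, and in the second row at b = 10%. The error can therefore go either way.

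**Same patients, two definitions.** In 200,000 simulated trials, six patients were drawn per level and both definitions were applied to them. Proportion of trials with a different stopping level:

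| Comparison | b | 1–5% | 2–10% | 5–45% |
|---|---|---|---|---|
| Descriptive Analysis v Sample Size Calculation | 0 | 0.043 | 0.145 | 0.587 |
| | 5% | 0.105 | 0.213 | 0.583 |
| | 10% | 0.210 | 0.309 | 0.596 |
| Sample Size Calculation v Analysis Variables | 5% | 0.070 | 0.098 | 0.142 |
| | 10% | 0.183 | 0.223 | 0.284 |

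**The case against.** Three arguments on the other side deserve an answer.

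**Relatedness may be implied.** Study hypothesis and Sample Size Calculation speak of toxicity, and elsewhere the endpoint is the toxicity of carbon ion radiotherapy, for example "The primary endpoint is acute toxicity of carbon ion radiotherapy observed within 30 days of study treatment". The later sections could simply spell out what the earlier ones assume. If the word unpredictable is also set aside as garbled text, only Descriptive Analysis is out of line. This does not hold up. Descriptive Analysis tabulates all toxicities by their relation to treatment, so in this article the word does not imply relatedness. The word unpredictable also remains in the primary-endpoint text. Even if the argument were granted, the reversibility conflict would stay, with the b = 0 discordance of 4.3%, 14.5% and 58.7%.

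**Context favours the irreversible wording.** It stands beside the decision rule, while the broad wording sits in a section on descriptive tables. That is a fair guess at the intention. But Descriptive Analysis presents its wording as the definition for the study, and Sample Size Calculation would still differ from Analysis Variables, which names the primary endpoint.

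**The sizes are assumed, and the largest rest on a harsh scenario.** This stands. The carbon-ion dose-escalation study described in the Background reported no severe treatment-associated effects in 24 patients. It used 15 fractions rather than four, so it does not fix the risk here, but it lends no support to 45%. With unrelated events in only 1–2% of patients, Sample Size Calculation and Analysis Variables disagree in about 1–2% of low-risk trials. The low-risk rows should be read first.

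**Conclusion.** The concern holds and should be corrected before any escalation decision. The article contradicts itself on the one quantity that drives escalation and the MTD; this is not detail left to an analysis plan. The contradiction rests on the text and needs no assumed rates.

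Its practical size does need them. Between the broadest wording and the one beside the escalation rule, the stopping level differs in about 4% of trials if related grade 4 events are rare and unrelated ones absent. The figure is 10–31% across the two lower-risk scenarios with unrelated events in 5–10% of patients, and close to 60% if related grade 4 risk climbs to 45%. These figures assume that half of grade 4 events are irreversible and none is unpredictable. They illustrate the range and are not forecasts.

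**What to change.** Adopt one DLT definition and use it word for word in Study hypothesis, Sample Size Calculation, Analysis Variables and Descriptive Analysis.

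- The sponsor decides whether irreversibility is a criterion and, if so, how it is judged by day 30.
- The sponsor decides whether unpredictable is a criterion; if it is kept, define it.
- Apply the possible, probable or definite relatedness rule throughout.

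Two secondary clarifications, which are not part of the contradiction, fit the same amendment. Run the window from the first fraction to day 30 after the last; at present the text says "For observation of DLT, patients are observed for 30 days after study treatment" without a start. Write grade 4 or higher, so that a related death counts.

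The cost is one wording amendment with no new assessments. The maximum of 33 patients is unchanged. A broader definition may call for more second cohorts within that cap: expected patients per visited level are 3 + 3[1 − (1−p)³], which is 3.4 at a DLT risk of 5%, 3.8 at 10% and 4.5 at 20%.

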### Statistical Methods

#### Sample Size Calculation

The calculation of sample size for the PROMETHEUS-01 trial is based on the traditional dose escalation scheme. DLT are considered any irreversible Grade 4 toxicity classified by CTCAE version 4.0 after study treatment.

Patients are treated in cohorts of three each receiving the same dose.

For observation of DLT, patients are observed for 30 days after study treatment. If the last patient of the cohort is observed 30 days after study treatment, patients of the next cohort may be recruited.

If none of the three patients shows a DLT, the next cohort of three patients receives the next higher dose as described above.

Otherwise, if at least one patient of the cohort develops a DLT (1/3), a second cohort of three patients is treated at the same dose level without escalating the dose.

If exactly one out of the six patients (1/6) treated exhibits DLT, the trial continues as planned at the next higher dose level.

If two or more patients out of the six exhibit a DLT, the dose escalation stops at that level and the next lower level is considered as the MTD. When the escalation has stopped, additional patients will be treated at the MTD to a total of nine patients.

This trial is conducted to choose the MTD of carbon ion radiotherapy between five dose levels. Therefore the sample size at maximum is 33 patients (4 dose levels with at maximum 6 patients and 9 patients at the MTD).

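### As worded, the escalation rule treats three more patients at a dose level after two or three DLTs in the first three, when stopping is already certain

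*Protocol article*

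**What the plan says.** The rule stands in the protocol article under Statistical Methods, Sample Size Calculation. The design "is based on the traditional dose escalation scheme", with cohorts of three at a common dose. Its steps are:

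- **No DLT in three:** "If none of the three patients shows a DLT, the next cohort of three patients receives the next higher dose".
- **Any other result:** "if at least one patient of the cohort develops a DLT (1/3), a second cohort of three patients is treated at the same dose level". The sentence opens as the alternative to a DLT-free cohort, so its words take in one, two or three DLTs. Its bracket gives only one in three.
- **One DLT in six:** "If exactly one out of the six patients (1/6) treated exhibits DLT, the trial continues as planned at the next higher dose level".
- **Two or more in six:** "If two or more patients out of the six exhibit a DLT, the dose escalation stops at that level", and the level below becomes the MTD.

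No sentence says what happens when two or three of the first three patients have a DLT, other than the one that opens a second cohort.

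Two further statements matter. On timing: "If the last patient of the cohort is observed 30 days after study treatment, patients of the next cohort may be recruited". On severity, the Study hypothesis section says: "Unacceptable toxicity (DLT) is defined as any irreversible grade 4 toxicity during a time frame of 30 days". The Analysis Variables and Descriptive Analysis sections word the DLT more loosely, but it is grade 4 in both.

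**The concern.** The stop criterion counts DLTs among six patients and is reached at two. If two or three have already occurred in the first three, nothing that happens in the next three can bring the count below two. The rule as worded nevertheless sends three more patients to that dose.

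What is at stake is patient safety, not the choice of MTD. These patients would be treated at a level whose rejection is certain, with a grade 4 and possibly irreversible toxicity as the event being counted. The exposure is also avoidable: because of the 30-day wait, the first cohort's count is known before the fourth patient is treated.

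**Working it through.** **Inputs.** From the protocol: cohorts of three, five dose levels, the four rules above, and a stated maximum of 33. The true DLT risk *p* at a level is not given, so it is an assumption and is varied.

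**1. The plan's own figure.** Four levels at six patients plus nine at the MTD: 4 × 6 + 9 = 33. Enumerating all paths through the five levels also gives 33, both as written and with the corrected rule.

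**2. Can the second cohort change the decision?** Add 0, 1, 2 or 3 further DLTs to the first cohort's count.

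- Two in the first three: total in six is 2, 3, 4 or 5.
- Three in the first three: total in six is 3, 4, 5 or 6.

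Every total is at least two, so every outcome stops escalation.

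**3. How often does this arise at one level?** With X ~ Bin(3, *p*):

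- P(X ≥ 2) = 3*p*²(1 − *p*) + *p*³. At *p* = 0.30 this is 3 × 0.09 × 0.70 + 0.027 = 0.189 + 0.027 = 0.216.
- Further DLTs expected in a needless cohort: 3*p*.
- Expected patients at a level during escalation: as written 3 + 3·P(X ≥ 1); corrected 3 + 3·P(X = 1).

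| *p* | P(X ≥ 2) | Further DLTs if it happens (3*p*) | Patients per level, as written | Patients per level, corrected |
|---|---|---|---|---|
| 0.05 | 0.7% | 0.15 | 3.43 | 3.41 |
| 0.10 | 2.8% | 0.30 | 3.81 | 3.73 |
| 0.20 | 10.4% | 0.60 | 4.46 | 4.15 |
| 0.30 | 21.6% | 0.90 | 4.97 | 4.32 |
| 0.40 | 35.2% | 1.20 | 5.35 | 4.30 |
| 0.50 | 50.0% | 1.50 | 5.63 | 4.13 |

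Given that a needless cohort opens, the chance of at least one more DLT is 1 − (1 − *p*)³: 66% at *p* = 0.30 and 88% at *p* = 0.50. The share of second cohorts opened with the decision already fixed, P(X ≥ 2)/P(X ≥ 1), is 0.216/0.657 = 33% at *p* = 0.30 and 0.500/0.875 = 57% at *p* = 0.50.

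**4. How often over a whole trial?** A level is passed with probability P(X = 0) + P(X = 1)·P(X = 0), the same under both rules (0.494 at *p* = 0.30). At most one level in a trial can produce the event, because the trial then stops. The probability is therefore the sum over levels of (chance of reaching the level) × P(X ≥ 2).

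For assumed risks of 5/10/20/30/45%:

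- Chance of reaching each level: 1, 0.973, 0.882, 0.625, 0.309.
- P(X ≥ 2): 0.007, 0.028, 0.104, 0.216, 0.425.
- Products: 0.007 + 0.027 + 0.092 + 0.135 + 0.131 = 0.39.

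That is 3 × 0.393 = 1.18 needlessly treated patients and 0.36 further DLTs per trial on average. Other assumed curves give:

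| Assumed DLT risk, steps 1 to 5 | Trials opening a needless cohort |
|---|---|
| 5% throughout | 3.4% |
| 2/4/6/8/10% | 5.8% |
| 1/2/5/10/15% | 8.9% |
| 10% throughout | 11.6% |
| 5/10/20/30/45% | 39.3% |

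**The case against.** The strongest reply is that this is a slip of wording. The bracket says one in three, and the protocol repeatedly calls the scheme traditional, so the authors probably meant exactly one DLT. That is plausible, but it does not rescue the text. Under the narrower reading no sentence covers two or three DLTs in three, and the words and the bracket of one sentence still disagree. The protocol uses the word *exactly* for one in six two sentences later and does not use it here.

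Three other points stand in part.

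- **The stop sentence is worded on six patients.** Strictly, after two DLTs in three the rule has not yet been applied. It is more accurate to say that its threshold has been reached and stopping is certain. The conclusion is the same.
- **DLT risks may be low.** The definition is narrow. The Background describes an earlier carbon ion escalation to 79.5 Gy E without severe treatment-related side effects. That study used 15 fractions against four here, so it does not fix the risk, but low values belong in the range. At low risk the event is uncommon, and the 39% figure should not be quoted alone.
- **Stopping within a second cohort** once the level's second DLT is seen would be a new rule and goes beyond reconciling the two sentences. It is sensible but optional.

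**Conclusion.** The point holds and should be corrected before patients are treated under this rule. On its literal reading, the protocol opens a second cohort that cannot affect the escalation decision. On the reading its bracket suggests, it gives no instruction for two or three DLTs in three.

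The logical part needs no assumption. The size depends on DLT risks that the documents do not give, and on independent patients with a common risk within a level. It ranges from about 3% of trials to about 39% over the curves examined, with three patients treated needlessly each time. The MTD decision, the chance of passing a level and the maximum of 33 are unaffected. The case for changing it rests on exposure to grade 4 harm without any gain for the decision.

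**What to change.** In Sample Size Calculation, make two small edits:

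1. Open a second cohort of three at the same level only if exactly one of the first three patients has a DLT.
2. Reword the stop sentence so that two or more DLTs at a level, whether among the first three or among six, end escalation there and make the next lower level the MTD.

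Optionally, add that enrolment to a second cohort ends as soon as the level's second DLT is seen.

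The cost is one or two sentences. MTD selection and the maximum of 33 stay as they are. Expected patients at a level fall, for example from 4.97 to 4.32 at a 30% DLT risk and from 5.63 to 4.13 at 50%. All that is given up is extra toxicity data at a dose already certain to be rejected.

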#### Analysis Variables

Primary endpoint is the MTD chosen between the five dose limits based on the traditional dose escalation scheme. Any unpredictable of irreversible grade 4 toxicity possibly, probably or definitely related the study treatment occurring 30 days after completion of study treatment is considered as dose limiting toxicity.

Secondary endpoints are the collection of safety data on the dose levels used in this trial as well as response, progression-free survival, and overall survival.

#### Analysis Populations

The Analysis set for primary endpoint consists of all patients treated at least once with the study treatment. A total of five analysis sets (one per dose level) will be considered.

Analysis set for secondary endpoints: All patients will be included for analysis for secondary endpoints treated at least one with the study treatment. Additionally, a total of five analysis sets (one per dose level) will be considered to determine any differences in secondary endpoints between the 5 dose levels.

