However, treatment options for patients with advanced staged HCC are limited and this patient group is associated with a poor prognosis [13]. In the past, no systemic chemotherapeutic treatment regimen has improved outcome in patients with advanced HCC [14-16]. New substances addressing single molecular targets, such as EGFR-inhibition with cetuximab, have not demonstrated convincing results [17]. Only recently, however, the multi-kinase inhibitor sorafenib (Nexavar^®^) has been shown to be effective in patients with HCC: In the multicenter SHARP trial (Sorafenib Hepatocellular Carcinoma Assessment Randomized Protocol), an increase in OS in patients with advanced HCC from a median of 7.9 months in the placebo group to 10.7 months in the sorafenib group could be demonstrated [18]. The study included 602 patients in a double-blind setting, and treatment with sorafenib was performed with 400 mg bid or placebo. Although OS and time to radiological progression were increased significantly, time to symptomatic progression (determined by the Functional Assessment of Cancer Therapy-Hepatobiliary Syndrom Index 8 (FHSI8) questionnaire or the occurrence of unacceptable adverse events or death) was not changed. Moreover, according to the RECIST-criteria, most controlled patients only showed stable disease in imaging, and only 2 out of 229 patients treated with sorafenib showed a partial response of the HCC; no complete remissions were observed.

Another randomized phase III trial evaluating efficacy and safety of sorafenib in patients with advanced HCC was performed in the Asia-Pacific region, and also demonstrated good tolerability of sorafenib and an increase in OS from 4.2 months to 6.5 months [19]. Again, time to symptomatic progression was unaltered by sorafenib, and the vast majority of patients controlled with sorafenib showed stable disease, with only 5 out of 150 partial responses and no complete remissions.

Therefore, this group of patients with advanced HCC is still characterized by unsatisfactory outcome, and treatment optimization is needed.

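### The primary-endpoint set is everyone treated at least once, so a partly treated or early-lost patient can stay in the 3+3 denominator without a DLT and bias the MTD upward

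*Protocol article*

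**What the plan says.** Under Analysis Populations the primary set is defined as follows: "The Analysis set for primary endpoint consists of all patients treated at least once with the study treatment". It is then split by level: "A total of five analysis sets (one per dose level) will be considered". The secondary endpoints use the same treated-once criterion, so the article names no separate DLT-evaluable set. Analysis Variables makes the MTD the primary endpoint. Table 1 gives four fractions at every level, so one fraction in four is enough to enter the set.

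The dose decision is described under Sample Size Calculation:

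- Cohorts: "Patients are treated in cohorts of three each receiving the same dose".
- First decision: "If none of the three patients shows a DLT, the next cohort of three patients receives the next higher dose as described above". With at least one DLT in three, three more patients are treated at the same level.
- Second decision: exactly one DLT among six treated patients continues the escalation; two or more stop it.
- Observation: "For observation of DLT, patients are observed for 30 days after study treatment".
- Gate: "If the last patient of the cohort is observed 30 days after study treatment, patients of the next cohort may be recruited".
- Maximum sample size: 33, from four levels of six plus nine at the MTD.

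The DLT window is worded in several ways. Analysis Variables ties it to the end of the course (toxicity "occurring 30 days after completion of study treatment is considered as dose limiting toxicity"), and Descriptive Analysis does much the same. Trial Duration, Study hypothesis and Sample Size Calculation refer to 30 days, or to the time after study treatment, without requiring completion.

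**The concern.** The 3+3 rule reads zero DLTs in three as evidence about three patients who received the dose and were watched through the window. A patient who stops after one fraction, withdraws, or dies of tumour before day 30 supplies less than that. The treated-once set nevertheless keeps that patient among the three or six, and a patient with no observed DLT has not shown one. A missed DLT can only reduce the count, so the error runs one way: the DLT rate is understated, and the trial can escalate past a level it should have stopped at.

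The gate does not close the gap. It names the last patient of the cohort and is silent on the other two.

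The completion wording adds to the problem. Under Analysis Variables and Descriptive Analysis, taken literally, a patient who stops early because of toxicity may never enter a DLT window, yet still belongs to the set.

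**Working it through.** **The plan's own figure.** 4 × 6 + 9 = 33. The longest path that stops at level 5 gives the same total: 6 + 6 + 6 + 9 + 6 = 33. The stated maximum reproduces exactly and contains no allowance for non-evaluable patients.

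**Escalation probability under the stated rule.** Let p be the true DLT risk at a level; the article gives no value, so a range is used. The level is escalated on 0/3, or on 1/3 followed by 0/3:

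P = (1−p)³ + 3p(1−p)² × (1−p)³

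**One of the first three gives no DLT information and is kept as a non-event.** Two patients are informative, and a second cohort, if needed, is complete:

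P₁ = (1−p)² + 2p(1−p) × (1−p)³

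| p | P, all three informative | P₁, one uninformative | Rise (points) |
|---|---|---|---|
| 20% | 0.709 | 0.804 | 9.5 |
| 30% | 0.494 | 0.634 | 14.0 |
| 40% | 0.309 | 0.464 | 15.4 |
| 50% | 0.172 | 0.313 | 14.1 |

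At p = 0.4: P = 0.216 + 0.432 × 0.216 = 0.309, and P₁ = 0.36 + 0.48 × 0.216 = 0.464.

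**Averaged over trials.** Suppose a share q of DLTs goes unobserved and is counted as none. Then p is replaced by p(1−q) in the first formula. The article gives no q, so 5-20% is an assumed range.

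| p | q = 0 | q = 5% | q = 10% | q = 20% |
|---|---|---|---|---|
| 30% | 0.494 | 0.525 | 0.557 | 0.622 |
| 40% | 0.309 | 0.343 | 0.378 | 0.454 |

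The rise is 3.1 to 12.7 points at p = 30% and 3.4 to 14.5 points at p = 40%, or about 3 to 15 points overall.

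**How often a cohort could be affected by an early death.** The time at risk is taken as 34 to 46 days: four treatment days, three gaps of 0 to 4 days each (Treatment Planning does not allow interruptions above 4 days), plus 30 days. Survival is assumed exponential.

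- From a median m in months: death per patient = 1 − exp(−ln2 × w/m), with w = 34/30.4 to 46/30.4 months.
- From 2-year survival S: death per patient = 1 − S^(days/730).
- At least one death in a cohort of three = 1 − (1 − d)³, where d is death per patient.

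| Source (Background) | Death per patient | Cohorts with at least one |
|---|---|---|
| 2-year survival 66% and 62%, proton series | 1.9-3.0% | 5.6-8.6% |
| Control median 7.9 months | 9-12% | 25-33% |
| Control median 4.2 months (the trial reporting "an increase in OS from 4.2 months to 6.5 months") | 17-22% | 43-53% |

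These figures cover deaths only. The article gives nothing from which to estimate withdrawal or incomplete treatment.

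**Enrolment if non-evaluable patients are replaced.** 33/0.95 = 34.7, so 35; 33/0.90 = 36.7, so 37; 33/0.80 = 41.25, so 42.

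**The case against.** The strongest reply is that no sentence in the article says a partly treated or early-lost patient is scored as free of DLT. That stands: it is an inference from the analysis set read with the escalation rule. The article does say that patients are observed for 30 days, and if the last patient of a cohort is lost, the gate is literally unmet. But the set is a stated rule, not an omission, and neither the gate nor the observation sentence says how an earlier patient who was not observed is to be counted.

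A reader might infer that nobody is replaced. The documents do not support that. The article is silent, it condenses a full protocol that is not shown, and a replacement rule may exist there. A reader might also infer that a patient who stops early can never score a DLT. That follows only from the completion wording in Analysis Variables and Descriptive Analysis; under the other three sections such a patient can.

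On size, 46% against 31% is conditional on one uninformative patient in the first cohort and is not the error rate of the design. The sorafenib control medians come from systemic-therapy trials, whereas this trial requires liver-confined disease and a Karnofsky score of at least 60, so they are an upper range. A patient who dies on day 25 was observed for 25 days, so treating every early death as no information overstates the loss. Conversely, the proton series may be more favourable than this population.

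Finally, treated at least once is not wrong in itself: it keeps DLTs that occur in partly treated patients. The defect is using it without an evaluability condition for the dose decision.

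**Conclusion.** The point holds at moderate severity; it is not a must-fix. The primary-endpoint set, as written, admits patients who did not complete the course or the 30-day window. Combined with the escalation rule, this can bias the MTD only upward. One uninformative patient among the first three raises the escalation probability from 31% to 46% at a true DLT risk of 40%, and from 17% to 31% at 50%. With an assumed 5-20% of DLTs unobserved, the average rise at 30-40% risk is about 3 to 15 points.

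How often this happens is not known from the article. Early death alone could touch about 6-9% of cohorts, with 25-53% as a pessimistic range. Both rest on exponential survival and on borrowed survival figures. The conclusion also assumes that the full protocol contains no evaluability or replacement rule. If it does, Analysis Populations contradicts that rule and should be brought into line with it.

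**What to change.** 1. In Analysis Populations, base dose decisions and the MTD on DLT-evaluable patients: those with a DLT after the first fraction, or those who received the full assigned course and were observed to day 30 after it.
2. In Sample Size Calculation, state that non-evaluable patients are replaced before the cohort decision, and extend the gate to all patients of the cohort. If the full protocol already says this, align the text with it.
3. State 33 as the maximum number of evaluable patients, with expected enrolment of about 35 to 37 at 5-10% non-evaluable (42 at 20%).
4. Keep the treated-at-least-once set for the safety tables.
5. Reconcile the DLT window wording in Trial Duration, Study hypothesis, Sample Size Calculation, Analysis Variables and Descriptive Analysis, so that it is clear how toxicity in a patient who stops early is counted.

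The cost is a wording change, a few replacement patients, and some delay in cohorts where a replacement is needed.
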